# Summary of the Study STOPDAPT ShorT and OPTimal duration of Dual AntiPlatelet Therapy study after everolimus-eluting cobalt-chromium stent

[Exploratory study to evaluate the safety of reduction of thienopyridine treatment period to 3 months after implantation of Cobalt-Chromium everolimus-Eluting Stents (XIENCE Prime™)]

**Summary of the Study:** Patients who received PCI using drug-eluting stent XIENCE Prime™ are enrolled serially, if the doctor in charge judged that the period of postoperative thienopyridine therapy can be reduced to 3 months. Thienopyridine treatment is discontinued at 3 months after stent implantation, and incidences of cardiovascular events and bleeding events at 12 months after surgery are evaluated.

Since this study is aimed at evaluating the real clinical situation, no exclusion criteria are defined.

Patients who have received any drug-eluting stents other than cobalt-chromium everolimus-eluting stent(XIENCE/PROMUS™) in the past should be excluded.

- **Study design:** Multicenter prospective registry
- **Primary Endpoint:** Composite endpoint of cardiovascular death at 12 months, myocardial infarction (MI), stroke (ischemic and hemorrhagic), stent thrombosis (Definite stent thrombosis not resulting in MI) and serious bleeding (TIMI Major/Minor).
- **Primary endpoint evaluation:** Exploratory assessment is made after 3-month thienopyridine treatment on the achievement of the performance goal calculated based on the incidence of the primary endpoint at 12 months obtained from the everolimus-eluting stent (XIENCE™) group in the RESET study, in which 90% of the patients were treated with thienopyridine for at least 1 year.
- **Target sample size:** 1500 patients
- **Principal investigator:** [name] Department of Cardiovascular Medicine, Kyoto University
- **Clinical study managers:**

|                                                                                        |                                                                                                                                                                 |
|----------------------------------------------------------------------------------------|-----------------------------------------------------------------------------------------------------------------------------------------------------------------|

### **LIST OF ABBREVIATIONS (COMMON EXAMPLES)**

---

| Abbreviation | Description                   |
|---------------------|--------------------------------------|
| DES                 | Drug Eluting Stent                   |
| BMS                 | Bare-Metal Stent                     |
| DAPT                | Dual AntiPlatelet Therapy            |
| CABG                | Coronary Artery Bypass Graft         |
| PCI                 | Percutaneous Coronary Intervention   |
| EES                 | Everolimus-Eluting Stent             |
| LMCA                | Left Main Coronary Artery            |
| eGFR                | estimated Glomerular Filtration Rate |
| ECG                 | Electrocardiogram                    |
| MI                  | Myocardial Infarction                |
| ST                  | Stent Thrombosis                     |
| ACS                 | Acute Coronary Syndrome              |
| QCA                 | Quantitative Coronary Angiography    |
| TLR                 | Target Lesion Revascularization      |
| TVF                 | Target Vessel Failure                |
| TVR                 | Target Vessel Revascularization      |

---

## 1. STUDY OBJECTIVE

Safety of reduction of thienopyridine treatment period to 3 months after implantation of Cobalt-Chromium everolimus-eluting Stents (XIENCE Prime™) will be evaluated in an exploratory manner.

## 2. BACKGROUND AND RATIONALE

The first-generation drug-eluting stents (DES), sirolimus-eluting stent (sirolimus-eluting stent: SES) and Paclitaxel-eluting stent (paclitaxel -eluting stent: PES), have achieved a remarkable outcome with reduction of the restenosis rate at 1 year after coronary stent implantation to  $\leq 10\%$ , and DESs are currently used in the majority of percutaneous coronary interventions (PCI) (References 1 and 2). On the other hand, as a problem associated with the first-generation drug-eluting stents, incidence of late-onset adverse events, including very late stent thrombosis and late restenosis, occurring after 1 year postoperatively, which were rarely associated with conventional bare-metal stents (BMS) has been pointed out, although not frequently (References 3 and 4).

Thienopyridine antiplatelet agents (platelet P2Y12 receptor antagonists) have markedly inhibited incidence of stent thrombosis, when they were combined with aspirin for 1 month after implantation of BMS (References 5 and 6). On the other hand, combination of aspirin with thienopyridine (dual antiplatelet therapy: DAPT) for more than 1 year after BMS implantation is frequently used to prevent very late stent thrombosis in the current clinical practice. In the RESET (Randomized Evaluation of Sirolimus-eluting versus Everolimus-eluting stent Trial) study, which was carried out in clinical practice in Japan, DAPT was performed for at least 1 year in 90% of the patients (Reference 7). DAPT for 1-year is recommended in the labeling of XIENCE Prime™ that is an improvement from everolimus-eluting stent that is currently most widely used in Japan. However, there has been no report showing that long-term thienopyridine treatment for at least 1 year reduces incidence of serious cardiovascular events, such as late adverse event and death after DES implantation, myocardial infarction (MI) and stroke. In addition, severe bleeding complication such as cerebral hemorrhage by prolonged DAPT is detrimental to the patients. To clarify the optimal duration of DAPT after implantation of DES is very important issue for patients who received DES implantation. Large-scale observational studies or small-scale randomized comparative studies size have demonstrated that thienopyridine treatment for 6 months (References 8-10) or for at least 12 months (Reference 11) does not reduce incidence of serious cardiovascular events. To evaluate the efficacy of DAPT for 6 months or for at least 12 months, large-scale studies, such as ISAR-SAFE (The Intracoronary Stenting and Antithrombotic Regimen: Safety And Efficacy of 6 Months Dual Antiplatelet Therapy After Drug-Eluting Stenting) and DAPT (Dual Antiplatelet Therapy) are ongoing (References 12, 13). In addition, we recently reported that a 4-month landmark analysis in 6309 patients enrolled in the CREDO-Kyoto (Coronary Revascularization Demonstrating Outcome Study in Kyoto) PCI/CABG Registry Cohort-2 who had received DES (mainly SES) implantation revealed that death in the following 3 years and incidences of MI and stroke showed no difference between patients who had been continuing thienopyridine treatment and those who had discontinued it at 4 months, while incidence of hemorrhagic complications tended to be higher in patients who had been continuing thienopyridine treatment. These results suggest that the optimal duration of DAPT after DES implantation may be shorter than 6 months (Reference 14).

With respect to Everolimus-eluting stent (EES), it has been associated with significantly lower incidence of early or late (within 1-year) stent thrombosis compared with the first-generation DES such as PES and SES and with BMS in large-scale observational study (Reference 4) and randomized comparative studies (References 15-17) and their meta-analyses (References 18, 19). In addition to these reports, recently EES received CE Mark in Europe for a DAPT length of minimum 3 months based on the observational study of

EES implanted patients demonstrated that no cases of stent thrombosis at 1-year were reported in patients who discontinued DAPT after 3 months post-EES implantation.

Considering that long-term DAPT obviously increases hemorrhagic complications compared to Aspirin monotherapy (References 10, 20, 21), it is desirable to reduce the duration of DAPT as far as possible, if long-term DAPT is not effective in inhibiting the incidence of serious cardiovascular events. Moreover, long-term DAPT enormously increases medical expenses. In this study, we planned an exploratory multicenter study to evaluate incidences of cardiovascular events and bleeding events at 12 months after stent implantation using an EES (XIENCE Prime™), which is associated with low risk of stent thrombosis, when thienopyridine therapy is discontinued at 3 months after surgery.

### **3. STUDY METHODS**

In this study, patients who received PCI using a drug eluting stent XIENCE Prime™ are enrolled serially, if the doctor in charge judged that the period of thienopyridine therapy can be reduced to 3 months.

thienopyridine treatment is discontinued at 3 months after stent implantation, and incidences of cardiovascular events and bleeding events at 12 months after surgery are evaluated. Since this study is aimed at evaluating the real clinical situation, no exclusion criteria are defined. Patients who have received any drug-eluting stents other than everolimus-eluting cobalt-chromium stent (XIENCE /PROMUS™) in the past should be excluded.

Exploratory assessment is made after 3-month thienopyridine treatment on the achievement of the performance goal calculated based on the incidence of the primary endpoint at 12 months obtained from the everolimus-eluting stent (XIENCE™) group in the RESET study, in which 90% of the patients were treated with thienopyridine for at least 1 year.

### **4. RULES FOR STUDY IMPLEMENTATION**

#### **4.1 Inclusion / Exclusion Criteria**

- In this study, patients who received PCI using a drug eluting stent XIENCE Prime™ are enrolled serially, if the doctor in charge judged that the period of thienopyridine therapy can be reduced to 3 months.
- Patients who have received any drug-eluting stents other than everolimus-eluting cobalt-chromium stent (XIENCE /PROMUS™) in the past should be excluded.
- Patients who have received administrations of antiplatelet drugs other than aspirin / thienopyridine should be excluded.

#### **4.2 Issued to be considered**

- Enrollment should be carried out after PCI with XIENCE Prime™ during the same hospitalization.
- The type and dose of aspirin are chosen according to the institute's guideline. The type and dose of thienopyridine should be equivalent to clopidogrel 75 mg/day. For patients who do not tolerate clopidogrel, this can be substituted with ticlopidine 200 mg/day.
- Administrations of antiplatelet drugs other than aspirin / thienopyridine are not acceptable.

- Patients can also be visited by the referring doctor, but Thienopyridine should be prescribed at the study institute.
- In discontinuing thienopyridine therapy, outpatient visit should be made in principle, and the discontinuation should be fully explained to the patient. F/U at 12 months after surgery should be performed at outpatient visit as far as possible. However, if the visit is impossible, F/U by telephone interview can be accepted. Incidence of any event should be recorded in the appropriate form.
- Although the planned follow-up period is 12 months, this can be prolonged if the Safety Evaluation Committee considers that safety must be followed up for a longer period.
- Acceptable time window for the discontinuation of thienopyridine therapy should be within  $\pm 1$  month.
- To ensure adherence to the administration schedule of thienopyridine, CRC of the study institute or equivalent staff communicates to the outpatient doctor the necessity of discontinuing the prescription of thienopyridine at the outpatient visit at 3 to 4 months after PCI, and confirms that the prescription of thienopyridine has been discontinued at the same visit.
- While initial enrollment is done by the investigator of each institute, data input, including PCI form, should be carried out by the institute's CRC or external CRC.
- Each institute should report the patients' background (age, sex, diagnosis, presence of diabetes mellitus, renal function, and target lesion) and the planned period of DAPT treatment even for the patients who receive XIENCE Prime™ implantation in the enrollment period and have not received any drug-eluting stents other than everolimus-eluting cobalt-chromium stent (XIENCE /PROMUS™) in the past, and who are not enrolled in this study.
- If planned staged PCI is scheduled, the patient will be enrolled after completion of all PCI. The last PCI should be the index procedure.
- Qualitative angiographic analysis and QCA analysis before and after Index procedure will be performed in 300 patients randomly selected. QCA analysis should be performed by core laboratory.
- For follow-up coronary angiography, the guideline of each institute should be followed. When coronary angiography is planned, recurrence of angina symptoms and results of evaluation of ischemia should be recorded in the clinical record before angiography.
- Recurrence of angina symptoms and results of evaluation of ischemia at the time of TLR are recorded in the clinical record.

### 4.3 Required examinations

The following examinations are mandatory. Other examinations may be added according to each institute's standards.

#### At Enrollment:

- Blood tests
  - In this study, hemoglobin and hematocrit concentrations should be measured, because TIMI definition is used to rate hemorrhagic adverse events.
  - Hemoglobin and hematocrit concentrations should be measured also when a hemorrhagic adverse event is suspected during the follow-up period.
  - WBC, RBC, hemoglobin, hematocrit, Plt, creatinine, blood glucose, HbA1c, total cholesterol, HDL cholesterol, LDL cholesterol, triglyceride

### 4.4 Follow-up period

In this study, information described in “6. Items to be investigated” will be collected at enrollment and at 12 months and recorded on the electronic Case Report Form (eCRF).

## **5. STUDY PERIOD**

This study will be carried out from August 2012 to July 2014, corresponding to the period from the beginning of enrollment to the scheduled completion of 12-month follow-up after PCI in the last enrolled patient. Although the enrollment period of this study is defined as within 1 year from August 1, 2012 to July 31, 2013, enrollment will be terminated when a total of 1200 patients are enrolled.

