## **8. DETERMINATION OF SAMPLE SIZE**

### **8.1 Sample size required for safety assessment on the primary endpoint**

The primary endpoint in this clinical study is a composite endpoint of cardiovascular death, myocardial infarction (MI), stroke, stent thrombosis and serious bleeding at 12-month follow-up. The event rate for the primary endpoint in this single arm study will be compared against a Performance Goal (PG) of 6.6% using an exact test through the binominal distribution.

This PG of 6.6% is derived by adding a delta to the assumed true event rate. Based on the historical XIENCE V data in the RESET trial (4% with a sample size 1559; reference 7), the one-sided 80% confidence limit is approximately 4.4%. To account for variability associated with the observed rate of 4% in the RESET trial, the true rate in this proposed trial is assumed to be 4.4%. With a delta taken to be 2.2% (50% of the base rate of 4.4%), the final PG is 6.6% (4.4%+2.2%).

Given the following assumptions:

One-sided alpha 0.025

True rate 4.4% (event during hospitalization were excluded)

PG 6.6%

An exact test through binomial distribution is used to calculate the p-value

Power approximately 95%

An effective sample size of 1455 is required. Take into consideration of dropout cases, a total of approximately 1500 patients is needed.

In addition, for evaluating the primary endpoint, complementary analysis using Cox proportional hazard model also will be performed, to take into account the differences in patient background of the everolimus-eluting Stent (XIENCE™) group in RESET study.

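### Section 5 closes enrollment at 1200 patients, but the Summary and Section 8.1 call for about 1500; under the 1200 cap the stated 95% power cannot be reached

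*Protocol*

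**What the plan says.** Three places in the protocol give a number for the size of the study.

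- **Section 5 (Study Period)** sets a one-year enrollment window, 1 August 2012 to 31 July 2013, and then adds that "enrollment will be terminated when a total of 1200 patients are enrolled".
- **The Summary of the Study** lists "Target sample size: 1500 patients".
- **Section 8.1 (Sample size)** states "An effective sample size of 1455 is required" and, after allowing for dropouts, "a total of approximately 1500 patients is needed". The assumptions are "One-sided alpha 0.025", a true 12-month event rate of 4.4%, and power of about 95%. The observed rate is "compared against a Performance Goal (PG) of 6.6% using an exact test through the binominal distribution".

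Section 10.4 says that the study runs until its target sample size has been enrolled, and Section 10.6 ends enrollment once all patients are in. Neither gives a number.

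**The concern.** Section 5 is the only place that ties a number to closing enrollment, and that number is 300 below the total in the Summary and Section 8.1. It is also 255 below the 1455 evaluable patients that Section 8.1 requires. Nothing describes 1200 as an interim, minimum or provisional figure.

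Two things are at stake. First, if Section 5 is followed, the power stated in Section 8.1 does not describe the study that is run. Second, in a single-arm study judged against a fixed performance goal, the final number of patients sets the event count that separates success from failure. A protocol with two totals leaves open which count applies and when enrollment should stop.

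**Working it through.** **Inputs.** From Section 8.1: performance goal p0 = 0.066, true rate p1 = 0.044, one-sided alpha = 0.025, exact binomial test, effective n = 1455, total about 1500. From Section 5: cap of 1200. The protocol states no dropout rate. Its two totals imply 1 − 1455/1500 = 3.0%, which is used below as an inferred value.

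**Method.** Few events mean success, so the critical count c is the largest integer with P(X ≤ c | n, p0) ≤ 0.025. Power is P(X ≤ c | n, p1).

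**Step 1: reproduce the plan's figure.** For n = 1455, c = 77, because P(X ≤ 77 | 0.066) = 0.0225 while P(X ≤ 78 | 0.066) = 0.0292. Power is P(X ≤ 77 | 0.044) = 0.954. The stated value of about 95% is confirmed, and Section 8.1 contains no arithmetic error here.

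**Step 2: apply the Section 5 cap.** With the inferred 3% loss, the evaluable number is 1200 × 0.97 = 1164.

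| Enrolled | Evaluable | Success if events ≤ | Actual alpha | Power at 4.4% | Chance of missing the goal at 4.4% |
|---|---|---|---|---|---|
| 1500 | 1500 (no loss) | 80 | 0.0245 | 96.3% | 3.7% |
| 1500 | 1455 (3% loss) | 77 | 0.0225 | 95.4% | 4.6% |
| 1200 | 1200 (no loss) | 62 | 0.0231 | 91.1% | 8.9% |
| 1200 | 1164 (3% loss) | 60 | 0.0239 | 90.5% | 9.5% |

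**Step 3: see whether any dropout rate rescues the cap.** Because dropout is not stated, take 1140 to 1200 evaluable (5% loss to none). Power then lies between 87.9% and 91.5%; it does not rise smoothly with n because c must be an integer. The best value for any n up to 1200 is about 91.5%. The smallest n that reaches 95% is 1398. The cap therefore cannot give the stated power even with complete follow-up.

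**Step 4: cross-check by normal approximation.** n = [(z₀.₉₇₅ √(p0(1−p0)) + z₀.₉₅ √(p1(1−p1))) / (p0 − p1)]² gives 1403 for 95% power. The same approximation gives power of 91.0% at n = 1200 and 90.1% at n = 1164, in line with the exact results.

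**The case against.** The case on the other side has four parts.

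- **The rest of the protocol points to 1500.** Section 10.4 continues the study to its target sample size, and the Summary attaches 1500 to that term. With Section 8.1, that leaves 1200 as a figure that appears once and may simply not have been updated. This is a fair reading, and it means the power is lost only if Section 5 prevails. But the document does not show that the figure is a leftover, and an outdated number in an enrollment stopping rule still has to be corrected.
- **The 3% dropout is an inference.** This is correct. The figures of 1164 patients, 60 events and 90.5% depend on it. The conclusion does not, since zero dropout still gives only 91.1%.
- **The loss is moderate.** This also stands. Power of 90% to 91% is respectable, and the exact test holds alpha below 0.025 at every n. The 4.4% rate was deliberately raised from the 4% observed in RESET. At a true rate of 4.0%, power is 98.1% with 1200 patients and 97.8% with 1164, against 99.3% with 1455. The protocol also calls the assessment exploratory.
- **A critical count that moves with n is a property of any exact test.** This is true and is no fault in itself. It matters here only because the protocol leaves n ambiguous.

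These points limit the size of the problem. None of them reconciles the two totals.

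**Conclusion.** The concern holds. The protocol gives two incompatible enrollment totals, and the one attached to closing enrollment is too small for the power claimed. Under the protocol's own assumptions, following Section 5 lowers power from 95.4% to 91.1% at best, and to 90.5% with the inferred 3% loss. At a true rate of 4.4%, the chance of wrongly failing the goal roughly doubles, from 4.6% to between 8.9% and 9.5%.

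The power loss alone would not make the design unsound. The stronger reason to correct the text is that one protocol, approved by the ethics committee of each participating institute, tells sites to stop at 1200 and also to aim for 1500. Whichever is done departs from part of it. The 3% dropout is inferred, and the size of the loss depends on the assumed true rate. That the totals conflict, and that 95% power is out of reach under the cap at the plan's assumed rate, does not depend on the dropout rate.

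**What to change.** Replace 1200 with 1500 in Section 5, so that it agrees with the Summary and Section 8.1. State that same number in Section 10.4, or refer there to Section 8.1, so that a single figure governs closure.

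If 1200 is the intended ceiling, keep Section 5 and change the other two places instead. Section 8.1 would give about 1164 evaluable patients and power of about 90%, with the dropout assumption written out, and the Summary target would become 1200.

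The first option is a one-number amendment and asks for no patients beyond the target already stated. The second costs only a restated sample size and power.

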## **6. ITEMS TO BE INVESTIGATED**

### **6.1 Planned Follow-up Periods**

The investigations in this study are performed at the following two time points:

- 1) At enrollment
- 2) Follow-up at 12 months after procedure (At the outpatient visit in principle, but telephone interview is also accepted.)

Acceptable time windows for follow-up visits are not established. However, follow-up at 12 months is to be performed within  $\pm 1$  month of the defined time point.

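### The single 12-month contact may be made at month 11, but the exact binomial primary test needs each patient's event status at 12 months

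*Protocol*

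**What the plan says.** - **Follow-up (Protocol 6.1).** Data are collected at two time points only: enrolment and 12 months after the procedure, the latter by outpatient visit or telephone. On timing, the section says "Acceptable time windows for follow-up visits are not established. However, follow-up at 12 months is to be performed within" one month of the defined point, on either side.
- **Primary test (Protocol 8.1).** The 12-month event rate is compared with a performance goal of 6.6% "using an exact test through the binominal distribution". The inputs are "One-sided alpha 0.025", a true rate of 4.4% and power of about 95%. The section concludes that "An effective sample size of 1455 is required", raised to about 1500 for dropout. A Cox model is added as a complementary analysis, to allow for background differences from the RESET stent group.
- **Calendar (Protocol 5).** "This study will be carried out from August 2012 to July 2014", with enrolment open from 1 August 2012 to 31 July 2013. The section also allows enrolment to close sooner, once a cap is reached.
- **Dates recorded (Protocol 6.2.2, items 1 and 2).** The case report form holds the date survival status was last confirmed and, separately, the date other events were last confirmed.

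**The concern.** An exact binomial test classifies every counted patient as event or no event at a fixed time. It has no means of using partial follow-up. Section 6.1 nevertheless lets a site make the only follow-up contact at month 11 and be fully compliant. No later contact is scheduled, so the last month may never be observed for that patient.

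Such a patient, if free of events at contact, must be counted as event-free, dropped, or handled by a rule that the protocol does not give. Under the first choice, events between contact and month 12 are lost from a test in which fewer events means success. At stake is the one-sided 0.025 error rate of the only primary test. An analysis plan can state a scoring rule, but it cannot recover follow-up that the protocol allowed sites not to collect.

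**Working it through.** **1. Reproduce the plan's figure.** Inputs from section 8.1: n = 1455, goal 6.6%, true rate 4.4%, one-sided alpha 0.025. Find the largest c with P(X ≤ c | n, 0.066) ≤ 0.025.

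- c = 77, since P(X ≤ 77) = 0.0225 and P(X ≤ 78) = 0.029.
- Power = P(X ≤ 77 | 1455, 0.044) = 0.954, which agrees with the stated 95%.
- Exact one-sided 97.5% upper limits: 77 events 6.57% (pass), 78 events 6.65% (fail).
- 1455 / 0.97 = 1500, so the dropout allowance is 3%.

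**2. Early contacts counted as event-free.** Assume a constant hazard over the 12 months and a mean unobserved time of L months per patient. The observed rate is then 6.6% × (1 − L/12), and the type I error is P(X ≤ 77) at that rate.

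| Mean time lost, L (months) | Observed rate | Expected events lost (1455 × 0.066 × L/12) | Type I error |
|---|---|---|---|
| 0 | 6.60% | 0 | 0.0225 |
| 0.1 | 6.545% | 0.8 | 0.027 |
| 0.25 | 6.46% | 2.0 | 0.036 |
| 0.5 | 6.325% | 4.0 | 0.056 |
| 1 | 6.05% | 8.0 | 0.122 |

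- L = 0.25 is the case of contacts spread evenly over months 11 to 13: half are early, by half a month on average (0.5 × 0.5 = 0.25).
- L = 1 requires every contact to fall exactly at month 11.
- If the hazard in the last month is half the average, the even-spread case behaves like L = 0.125 and the error is 0.029.
- At the design rate of 4.4%, the even spread loses 1455 × 0.044 × 0.25/12 = 1.3 events, and the worst case loses 1455 × 0.044/12 = 5.3.

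**3. Early event-free contacts dropped, early events kept.** Take the even spread at the design rate of 4.4%, with 727.5 patients contacted before month 12 and 727.5 after.

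- Early events: 727.5 × 0.044 × (1 − 0.5/12) = 30.7. Late events: 727.5 × 0.044 = 32.0.
- Denominator: 727.5 + 30.7 = 758.2.
- Observed rate: 62.7 / 758.2 = 8.3%, above the 6.6% goal although the true rate is 4.4%.

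So the direction of the bias depends on the scoring rule.

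**4. The calendar.** A patient treated on 31 July 2013 reaches 12 months on 31 July 2014, when the study period ends, so the whole late side of the window is lost. A patient treated on 1 July 2013 loses almost none of it, and those treated in between lose part. Patients treated before July 2013 keep all of it.

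**5. Kaplan-Meier limit as an alternative test.** With complete follow-up of 1455 patients, the plain Greenwood one-sided 97.5% upper limit is 6.52% at 78 events and 6.59% at 79. Both would pass, so the type I error is P(X ≤ 79 | 1455, 0.066) = 0.0375. The log-log limit is 6.57% at 77 and 6.65% at 78, the same cut-off as the exact test.

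**The case against.** The strongest reply is that scoring of incomplete follow-up belongs in an analysis plan, which is not shown, and that the form already records the last-confirmation dates needed for a censoring or completeness rule. That stands for the scoring rule. It does not cover the contact window, which is a protocol rule and determines which data exist.

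It can also be said that the conflict in 6.1 is editorial, because the second sentence narrows the first and the window in force is clear. This is largely right. The important defect is what that window allows.

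A reader might go further than the documents permit in four ways:

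- **That the protocol counts unobserved time as event-free.** No section says so. It is one possible scoring rule, and another rule reverses the bias.
- **That the study end leaves no room for late contact and pushes contacts early in general.** It affects only patients enrolled around July 2013, and nobody if enrolment closes before then.
- **That the roughly 45 dropouts add to the loss.** Section 8.1 sets them outside the effective 1455, so they cannot be added to a count based on 1455.
- **That Kaplan-Meier should replace the exact test.** With a plain Greenwood limit, the error rate of 0.0375 would be slightly worse than the 0.036 it was meant to cure.

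The Cox analysis does not settle the matter. It is complementary, and its stated purpose is background differences.

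**Conclusion.** The point holds in a limited form. Section 6.1 contradicts itself on windows and permits the only outcome contact at month 11. Section 8.1 fixes a test that needs status at month 12. If early contacts are scored as event-free, the type I error rises from 0.0225 to about 0.036 under an even spread of contacts, and the nominal 0.025 is already passed at a mean loss of 0.1 month (0.027). The figure of 0.122 is an outer bound that nothing in the protocol makes likely.

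These are sensitivity figures, not a forecast. They rest on a constant hazard, n = 1455, a true rate of 6.6%, an assumed spread of contacts, and a scoring rule that the protocol does not state. A lower hazard near month 12 shrinks them. The stated sample size itself reproduces and is not in question here. The change is worth making because it costs little and removes a dependence that later analysis can only partly repair.

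**What to change.** 1. In 6.1, delete the sentence that no windows are established. Require the 12-month contact at or after day 365, within 12 to 13 months, and count events through day 365.
2. In section 5, extend the study period to the end of August 2014, so that the last enrolled patients have the full window.
3. In 8.1, keep the exact binomial as the primary test. Add, as a sensitivity analysis for patients whose last confirmation is before day 365, a Kaplan-Meier estimate at day 365 with a log-log one-sided 97.5% upper limit set against the goal. Name the log-log limit explicitly and do not use the plain Greenwood limit. The dates in 6.2.2 are sufficient for this.

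The cost is one more month of study period and slightly later contacts. No scheduled visit or data item is added, and telephone contact is already accepted. The Kaplan-Meier estimate equals the simple proportion when follow-up is complete.
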